### **7.5.4 Replacement of Withdrawn Patients**

Up to 12 patients will be recruited, in order to have a sample size of at least 6 patients catheterized with NO-impregnated catheters and 6 patients catheterized with non-NO-impregnated catheters, who completed the study (see protocol).

## **8. STUDY CONDUCT DETAILED STUDY PLAN**

### **8.1 Screening & Enrolment procedures**

#### **8.1.1 Screening and Enrolment – Visit 1 (day 0)**

- Check patient eligibility (Inclusion/exclusion criteria)  
Enroll only patients who meet all inclusion criteria and none of the exclusion criteria
- Review study with the patient and obtain written informed consent
- Record demographics data and medical history
- Record concomitant medications
- Perform a full physical examination
- Perform urine test (microbiology and biochemistry), blood test for CBC, biochemistry, and coagulation: Prothrombin Time (PT), activated Partial Thromboplastin Time (aPTT), and International Normalized ratio (INR)
- Perform and record vital signs: temperature, blood pressure and heart rate
- Document any laboratory test done for medical reasons during the preceding month (blood tests, urinalysis etc.)

### **8.2 Randomization**

N/A

### **8.3 Study Treatment**

#### **8.3.1 Operation and Catheterization – Visit 2 (day 1)**

- Perform a full physical examination
- Perform and record vital signs: temperature, blood pressure and heart rate
- Catheter insertion
- Perform urine test (microbiology and biochemistry), blood test for CBC, biochemistry, and coagulation: Prothrombin Time (PT), activated Partial Thromboplastin Time (aPTT), and International Normalized ratio (INR)

#### **8.3.2 Hospitalization – Visit 2 continuation (day 2 - discharge day)**

- Perform a full physical examination
- Perform and record vital signs: temperature, blood pressure and heart rate
- Perform urine test (microbiology and biochemistry) , blood test for CBC, biochemistry, and coagulation: Prothrombin Time (PT), activated Partial Thromboplastin Time (aPTT), and International Normalized ratio (INR)

#### **8.3.3 Catheter Removal – Visit 3 (day 7-21±7)**

- Remove Catheter\*\*
- Perform a full physical examination
- Perform and record vital signs: temperature, blood pressure and heart rate
- Perform urine test (microbiology and biochemistry) , blood test for CBC, biochemistry, and coagulation: Prothrombin Time (PT), activated Partial Thromboplastin Time (aPTT), and International Normalized ratio (INR)
- Measure post-void residual urine volume

\*\* After catheter removal catheter specimens will be processed according to protocol (see appendix 1).

## 8.4 Follow-up Visits

### 8.4.1 Telephone call – Visit 4 (day 21±3)

- Perform a telephone call for follow-up and record any new medical conditions, AEs, or SAEs

### 8.4.2 Follow-up Visit - Visit 5 (day 30- 45)

- Perform a full physical examination
- Perform and record vital signs: temperature, blood pressure and heart rate
- Perform urine test (microbiology and biochemistry) , blood test for CBC, biochemistry, and coagulation: Prothrombin Time (PT), activated Partial Thromboplastin Time (aPTT), and International Normalized ratio (INR)

## 8.5 Unscheduled Visits

An unscheduled visit may be performed at any time during the study at the patient's request or as deemed necessary by the investigator. The date and reason for the unscheduled visit will be recorded. The following procedures and evaluations may be completed as deemed necessary by the investigator:

- Perform a full physical examination
- Perform and record vital signs: temperature, blood pressure and heart rate
- Perform urine test (microbiology and biochemistry) , blood test for CBC, biochemistry, and coagulation: Prothrombin Time (PT), activated Partial Thromboplastin Time (aPTT), and International Normalized ratio (INR)

## 8.6 Termination/Study Early Discontinuation

Treatment/study can be either temporarily or permanently discontinued. Criteria for discontinuation are specified in section 7.5

The reason for discontinuation of study will be documented in the source documents and captured on the CRF. In the event that the catheter is removed prematurely, end of treatment assessments (section 7.4) should be completed as close to the last date as possible.

If a patient is withdrawn because of an AE, the appropriate "Withdrawal Section" of the CRFs should be fully completed in addition to the AE module. ENOX BIOPHARMA should be informed of all patients who are withdrawn for this reason.

Documented attempts will be made to follow a patient who prematurely discontinues the study.

## **8.7 Emergency Code Breaking**

N/A

## **9. DESCRIPTION OF INVESTIGATIONAL MEDICINAL PRODUCTS/STUDY**

### **9.1 Foley Catheter Embedded with Nitric Oxide**

The catheters are manufactured and bought from Biometrix Ltd, an Israeli supplier. These catheters are approved for use in the Israeli health system (see appendix 2). The catheters are already sterile and ready to use.

For the study we will impregnate 18Fr catheters. This diameter was chosen follow consultation with the principal investigator of the study.

### **9.2 Impregnating Device**

To impregnate the NO gas into the catheter, a designated proprietary impregnating device is used. The impregnating device is a chamber that is connected to vacuumed pump and an NO gas container. The gas that is used is supplied by Maxima Ltd, Israel, which is responsible for its manufacturing. The gas, which is tagged and colored according to the israeli regulation, is stored at 20,000 ppm, concentration with 99.999% nitrogen purity - according to Good Manufacturing Practice (GMP) spirit and guidelines and ISO 9001.

### **9.3 Impregnating Process**

Catheters (see appendix 3) wrapped in their original sterile package are placed inside the impregnating chamber. After the chamber is tightly secured the vacuum pump is connected to the vacuum outlet of the chamber. Vacuum pump is then turned on, and the vacuum outlet is opened until the pressure reaches negative 10 psi. When required pressure is achieved the vacuum outlet is closed and the vacuum pump is turned off. Then the gas cylinder, containing 20,000ppm is turned open, while the regulator is open and is connected to the chamber. The NO gas, stored in purple cylinder is let flow into the impregnating chamber through the opened gas inlet, until the pressure reaches back to the level of 0 psi. The gas supply is closed from the gas cylinder, while the regulator and the process valve on the chamber are closed. The catheters are impregnated by incubation with 20,000ppm NO for at least 4 hours. Once impregnating is completed the "purge" outlet is opened, and air flows from condensed air (green cylinder) cylinder. During this time the regulator is directed to provide a very low pressure of 1-2 psi, during purging of at least 2 hours. Then the lid is released and the chamber is emptied from the loaded device

### **9.4 Sterilization/Validation**

During the entire impregnating process the catheters are kept in their original sterile packages. Therefore, at the end of the impregnating process the catheters are expected to remain intact and sterile.

In order to confirm that the catheters are not contaminated during the impregnating process, ENOX conducted a sterilization/validation test according to current GMP for medical devices. The tested catheters met all sterilization criteria and were found to be sterile (see appendix 4).

## 10. RISK ANALYSIS

In light of the low concentration expected to be released from the catheter, and in light of the short half-life of NO in the blood, we do not expect any severe and systemic side effects. However, low concentration of inhaled NO (5-40ppm) in some cases was found to be associated with decreased blood pressure, inhibition of platelet aggregation, and increased bleeding time [38-40]. In addition, NO may trigger local side effects such as erection, local skin irritation, and the formation of skin edema and erythema [41] . (See appendix 5 - table of possible adverse events related to NO-impregnated catheters).

To assess the risk associated with the use of NO-impregnated catheters, ENOX performed a pre-clinical safety study in NZW rabbits. No adverse effect and no safety concerns were raised in the conclusion of this study (see main content of the report in appendix 2 in the investigator brochure). ENOX chose to conduct the safety trial on rabbits and not on larger animals such as pigs for two main reasons: 1) the life habitat of pigs is unsterile by nature and may affect trial outcome, causing undesired manifestations that are not related to NO-impregnated catheters. 2) The anatomy of pigs' urethra is not ideal for catheterization over an extended period

Additional tests performed by ENOX include:

- Mechanical test, performed by degania silicone Ltd., Israel
- In vitro cytotoxicity test performed by Harlan Biotech, Israel (STUDY NO ENI/001/CTX)
- In vivo intradermal reactivity tests performed by Harlan Biotech, Israel (STUDY NO ENI/002/IRT)
- In vivo sensitization test performed by Phycher Bio Developpment, France (Harlan Project NO 41400562)
- In vivo safety trial for the NO-impregnated catheters performed by Harlan Biotech, Israel (STUDY NO ENI/003/EM)

ENOXs NO-impregnated catheter meet with all required criteria and was classified as non-cytotoxic, non-irritating and non-sensitizing device (see full reports in IB).

During the trial catheterized patients will be monitored daily (see protocol, section 6.1) through physical examination and vital signs measurements. In addition, blood tests will also be conducted in order to exclude any significant change in platelet counts, and biochemistry values (see appendix 5 - table of possible adverse events related to NO-impregnated catheters).

## 11. ASSESSMENT METHODS

### 11.1 Observational

- Proportion of patients (%) who prematurely discontinued the study for any reason
- Measure and compare the biofilm formation on the surface of NO-impregnated versus non-impregnated Foley catheters after indwelling for 7-21±7 days
- Measure and compare bacteriuria (by urine culture) for NO-impregnated versus non-impregnated Foley catheters prior to insertion, on catheter insertion day, every day during hospitalization, on catheter removal day, and 30-45 days after catheterization
- Compare occurrences of clinically significant UTIs following catheterization with NO-impregnated and non-impregnated Foley catheters.
- Record Different species of bacteria contaminations

### 11.2 Medical/Clinical Assessment

Initial demography/medical history form (complete questionnaire including AE and SAE will be provided).

#### **Physical Examination:**

A physical examination will be performed by a physician (either the principal investigator or a sub-investigator) on each visit. Body systems to be examined grossly include: General, Skin, Lymph Nodes, HEENT, Respiratory, Cardiovascular, Gastrointestinal, Neurologic and Musculoskeletal, and the Penis, Scrotum and Groin. New abnormal findings must be documented and should be followed by an investigator at the next scheduled visit.

#### **Vital Signs:**

Heart rate, blood pressure, and temperature will be performed and recorded.

#### **Adverse Events:**

Information regarding occurrence of AEs will be captured throughout the study and until the patients follow-up is complete.

Event duration (start and stop dates and times), severity, outcome, treatment and relation to study medication (causality) and if the event is regarded as SAE, will be recorded in the CRF.

AEs will be followed until day 30-45 of the study.

**Concomitant Medications:**

Concomitant medication given during the study will not lead to study treatment discontinuation.

All concomitant medication and concurrent therapies will be documented throughout the study until day 30 of the study.

The following information will be recorded: Dose, route, unit frequency of administration, and indication (if deemed relevant) for administration of medication. All concomitant procedures will be documented throughout the study until day 30 of the study, the reason for the procedure will be considered as AE/SAE, unless it was scheduled prior to study start.

**11.3 Clinical Laboratory Assessments/Evaluations****11.3.1 Blood Tests**

Blood tests as detailed in section 5.3.2 to this protocol will be recorded in the CRF and will be used for the study analysis.

Any other blood tests results (that were done for clinical reasons and not required for study) collected during the patient's treatment or study follow up will be recorded in the CRF and will be used for observational analysis.

**11.3.2 Bacteriological Tests****Detection of bacteria in urine:**

Urine tests for relevant bacteria will be performed according to the European Urinalysis Guidelines published by the European Confederation of Laboratory Medicine (ECLM) [42], in consultation with the microbiologist on site.

**Detection of bacteria on catheter**

Within removal of the catheter (1 hour maximum), cut the catheter into small 1-cm sections. 3 x 1-cm sections from each catheter will be analyzed per tests for biofilm formation as followed:

**Exterior catheter surface:**

Within removal of catheter (1 hour maximum), cut the catheter is to small sections of 1cm each. Then the catheter section is washed three times using 3 ml of sterile saline (0.9% wt/vol NaCl). After wash, the catheter section is

aseptically transferred to an LB agar plate, and rolled once on the plate. The plate is then incubated at 37°C for 24 hours.

### **Quantification of biofilm and Biofilm-forming bacteria:**

Quantitative measurement of bacterial biofilm and biofilm-forming bacteria will be determined by two methods: absorbance at 595nm using a spectrophotometer, and CFU measurement following sonication.

#### Spectroscopy:

A 1-cm section of the catheter is washed 3 times with saline and added to 1.5 ml of crystal violet dye (serves as an indicator of biofilm formation) previously diluted in water (1% wt/vol). After 15 minutes incubation the catheter section is washed three times with water and transferred to 2 ml of 95% ethanol to relinquish crystal violet bound to the surface of the catheter. Absorbance of each ethanol sample is read at 595 nm using a spectrophotometer.

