#### CFU measurements:

A 1-cm section of the catheter is washed 3 times with saline. Transfer each section to 2 ml of saline 0.9% and sonicate for 20 seconds (30KHz). CFU's are determined by plating each sample on blood agar after serial dilution with saline and incubation at 37°C overnight.

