## **22. APPENDICES**

### **Appendix 1**

**Microscopic Examinations:**

Upon removal, the indwelling urinary catheter will be cut into 1-cm sections and the balloon section. Samples for EM will be cut into two transverse sections. One section of the urinary catheter is collected into an individual 50ml vial. Each vial is labeled by study coordinator: No., Group No., patient No., date of removal & collection time.

Immediately following collection, all the vials are stored at 2-8°C until their transportation to microbiology lab for bacteriological analysis.

The other section of the indwelling urinary catheter is collected into an individual 50ml vial, containing fixative (supplied by sponsor) for EM.

Each vial is labeled by study coordinator: Group No., patient No., date of removal & collection time.

Immediately following collection, all the vials are stored at 2-8°C and transported to the microbiology laboratory. In case transportation is delayed the vials can be stored overnight at 2-8°C and transported the next day for microbial and biofilm analysis.

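### The crystal-violet biofilm assay has no unused-catheter blank, so any difference in dye uptake by the NO-exposed material is confounded with study group

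*Protocol*

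**What the plan says.** Section 11.3.2 of the protocol quantifies biofilm by two methods: "absorbance at 595nm using a spectrophotometer, and CFU measurement following sonication". The number of sections is fixed ("3 x 1-cm sections from each catheter will be analyzed per tests for biofilm formation as followed"), but not where along the catheter they are taken.

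The dye method is written out in bench detail: saline washes, 1.5 ml of 1% "crystal violet dye (serves as an indicator of biofilm formation", 15 minutes, water washes, elution in 2 ml of 95% ethanol. It ends with "Absorbance of each ethanol sample is read at 595 nm using a spectrophotometer". No blank, unused catheter section or background subtraction appears there or elsewhere in the protocol.

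Section 9.3 has the treatment catheters incubated in 20,000 ppm NO for at least 4 hours. The control catheters are not impregnated. Sections 6.1 and 7.1 allocate the first 6 patients to NO catheters and the next 6 to plain ones, without randomisation.

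Section 5.2 lists the between-group biofilm comparison as an observational endpoint. Section 13 (Observational Assessment) tests it with a two-sample t-test or rank-sum test at a two-sided 5% level.

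**The concern.** Retained crystal violet measures whatever holds the dye: bacteria and their matrix, other adherent cells or protein, and possibly the catheter material. An unadjusted reading adds these together.

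The material component is the clearest weakness. Every NO section is of one material and every control section of the other. If gas exposure changes dye uptake, all NO readings shift relative to all control readings, and the control group cannot correct this because it is the other material. Only unused sections of both types can separate a material effect from a biofilm effect.

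The second component is blood, clot or mucosal debris left on the surface after radical prostatectomy. It biases the comparison only if it differs between groups. That is possible, because the groups are sequential and dwell time is allowed to vary (7-21±7 days), but nothing in the documents shows that it does.

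At stake is whether a difference in absorbance can be read as a difference in biofilm. A blank has to be stained in the same run as the samples, so a later analysis plan cannot recover it.

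**Working it through.** **No stated figure to reproduce.** The protocol gives no absorbance SD, no expected difference and no power. Section 13.1 does not derive the 12 patients from a formula.

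**What a reading contains.** Write the mean absorbance in a group as B + H + M, where B is bacterial biofilm, H is non-bacterial adherent material and M is dye held by the catheter itself. The expected difference between groups is

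(B_NO − B_plain) + (H_NO − H_plain) + (M_NO − M_plain).

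An unused section of each type estimates M_NO and M_plain. Subtracting the matching blank removes the third term, provided that unused material takes up dye as the removed catheter's material does. It leaves the second term untouched, because an unused catheter carries no clot or debris.

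**Illustration of an uncorrected offset.** Inputs from the protocol are 6 per group and two-sided alpha 0.05. The assumed input is a background offset d between groups, in between-patient SDs, with no bacterial difference. The documents give no value for d, so a range is shown.

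For the t-test, df = 10, the critical value is 2.228 and the noncentrality is d × √(6/2) = 1.732d. The rejection rate is the probability that a noncentral t variable falls beyond ±2.228. The exact rank-sum test was simulated 20,000 times per row.

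| Offset d (SD, assumed) | Noncentrality | t-test rejects | Rank-sum rejects |
|---|---|---|---|
| 0 | 0 | 5.0% | 3.9% |
| 0.5 | 0.866 | 12.3% | 10.4% |
| 1 | 1.732 | 34.7% | 30.0% |
| 1.5 | 2.598 | 65.0% | 59.5% |
| 2 | 3.464 | 87.6% | 82.7% |

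If the offset is entirely material uptake and the blank removes it fully, the rates return to the first row.

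**Debris alike in both groups.** The same assumed lognormal debris term (log-mean 0, log-SD 0.8) was added to a unit-SD signal in both groups. With no true difference, rejection was 4.5% (t-test) and 4.2% (rank-sum), so there is no inflation. The cost is noise: t-test power for a true 2 SD difference fell from 87% to 56%.

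**Section position.** Positions are unspecified in both groups alike. This adds scatter and prevents stained and cultured sections from being paired within a catheter. It does not by itself create a directional bias.

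**The case against.** The protocol does not rely on dye alone. Sonication counts ("CFU's are determined by plating each sample on blood agar after serial dilution with saline and incubation at 37°C overnight") do not register clot or dye. The exterior surface is also cultured, with the section "aseptically transferred to an LB agar plate, and rolled once on the plate", and Appendix 1 sends a section into a vial "containing fixative (supplied by sponsor) for EM". These give evidence that does not depend on dye and could expose an absorbance difference without a bacterial one. Sections 17.1 and 17.2 place procedures under written SOPs and the bacteriology under a laboratory quality plan, so a blank may be run without being stated. How two observational measures are ranked can be left to the SAP. The endpoint is observational, and Section 13.1 disclaims statistical significance and power.

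Most of this stands, and it limits the point to a minor one. It does not dispose of it. The protocol sets out the dye step in full and gives no reference reading. The other assays do not correct the absorbance itself, and the protocol does not link the readings.

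Several stronger readings are tempting but not supported:

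- **That the bias favours the NO catheter because NO leaves less clot.** Section 10 lists "decreased blood pressure, inhibition of platelet aggregation, and increased bleeding time" for inhaled NO at 5-40 ppm, in some cases. Longer bleeding could equally leave more blood on the NO catheter, so the direction is unknown.
- **That the missing blank causes clot to be counted as biofilm.** An unused catheter has no clot to subtract.
- **That the catheters are assayed from a fresh surgical site.** That describes insertion. Section 8.3.3 removes them at day 7-21±7, and the sections are washed before staining.
- **That a lower absorbance would by itself be reported as biofilm prevention.** The protocol does not say so.
- **That CFU must be the sole deciding measure.** CFU counts only what grows in overnight culture, so this is a trade-off and not a correction of an error.

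**Conclusion.** The point holds in a limited form. As written, the dye assay cannot separate a change in dye uptake by NO-exposed material from a change in biofilm, because material and group coincide completely. Non-bacterial adherent material is a second possible contributor, and it matters for bias only if it differs between the groups.

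Whether either effect exists, how large it is and which way it runs cannot be determined from the documents. The rise from 5% to about 12–35% rests on an assumed offset of 0.5 to 1 SD. It shows how sensitive a 6-versus-6 comparison is to such an offset and is not an estimate for this trial.

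The consequence is confined to the absorbance part of one observational endpoint. The primary safety and tolerability conclusions do not depend on it. This is a cheap improvement of minor weight.

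**What to change.** Amend Section 11.3.2, with a matching line in Section 13, before the first catheter is removed:

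1. In each staining run, process one unused NO-impregnated and one unused plain section in the same way as the samples, and subtract the blank of the same catheter type. State that this corrects dye uptake by the material and not clot or debris.
2. Take the stained and the sonicated sections from adjacent positions, at the same fixed distances from the tip in every catheter.
3. Report absorbance at 595 nm as total adherent material and interpret it alongside sonication CFU, which dye uptake and clot do not affect.

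The cost is a few unused sections and reagents per run and a few lines of text. The downside is that a difference seen in absorbance alone can no longer be called a biofilm effect.
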